**Primary**		
1. Palliative care access and timing	**Results**	Access: Total case load, # identified PC, Timing: Typical timing of when first palliative care will be initiated for cancer and noncancer patients
2. Palliative care competency	**Learning**	End-of-life Professional Caregiver Survey (EPCS) – 20 items
3. Assignment completion / Change in practice	**Learning** **Behavior** **Results**	Checklist of completion of module specific assignments (study created survey) Change survey – 4 items

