#### Primary outcomes

1. Palliative care access and timing, measured based on self-reported: i) number of patients in caseload and number (calculated %) reported as Identified as requiring a palliative approach to care in last 3 months, ii) Typical timing of when PCP initiates a palliative approach to care for their cancer and non-cancer patients, respectively.2. Palliative care competency, measured by scores on the End-of-life Professional Caregiver Survey (EPCS). The EPCS is a 28-item scale developed to assess palliative care-specific educational needs within an interprofessional team related to three main subdomains: Effective Care Delivery (ECD 8-items); Patient and Family-Centered Communication (PFCC 12-items); and Cultural and Ethical Values (CEV 8-items) [24]. Each item is scored on a 5-point Likert scale ranging from 1 (lowest level of skill) to 5 (greatest level of skill). Items represent care-provider comfort with a variety of situations related to palliative and end-of-life care. The EPCS covers all eight domains of the national palliative care guidelines and core lessons of physician-specific and nurse-specific end-of-life education curricula in the USA. The EPCS exhibits strong internal consistency (alpha = 0.96). For the purposes of this study, we will exclude the CEV sub-domain items from the EPCS.3. Assignment completion and perceived change in practice, measured by number of module assignments attempted/completed (checklist) and reported change in thinking, behaviour, processes, and patient/family experience (Assignment Completion & Change Survey). This survey is a two-part, study-created questionnaire based on the CAPACITI module activities. Part A is unique to each module, asking participants to indicate the extent to which they were able to complete each of the session assignments for the module. Response options are: Have not started (1), Started but not completed (2), Completed (3). Part B contains four items assessing changes in thinking, behaviour, processes, and patient/family experience, respectively.

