### Statistical power /sample size

Sample size calculation is based on the assessment of the primary outcomes of Effective Care Delivery (ECD 8-items) subdomain on the End-of-life Professional Caregiver Survey (EPCS) and the palliative care identification variable (% of patients identified as requiring a palliative approach to care).

Previous work using the EPCS with nurses, physicians, and social workers identified a mean score of 3.6 for the ECD subdomain and a standard deviation (SD) of 1.0 (scale from 1 to 5) [24]. We assumed that a difference of 0.5 in SD (i.e., a delta of 0.5 or a half point on the scale) between treatment groups at T2 would be important to detect. Accounting for the cluster design, we estimate that the correlation between providers within teams was 0.15 and that each team would have a minimum of 4 members participate. Given a two-sided alpha of 0.05, a power of 80%, 192 providers from 48 teams would be required. This will also allow for detection of a 1-point difference increase of the % of patients identified as requiring a palliative approach to care (SD = 2).

We anticipate 100 PCP teams with an average of 4 members per team, in each module. The teams will be from across Canada and geographically diverse (e.g., rural, urban, and remote), which is critical to generating evidence on generalizability in diverse communities across the country.

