### Eligibility

To be eligible the “team” or individual must be community-based and willing to provide palliative care to their patients, defined as managing symptoms, addressing psychosocial needs, educating patients and families, and coordinating care. Teams need to include at least one prescribing clinician (e.g., primary care physician, nurse practitioner). Participates in CAPACITI can include physicians, nurses, social workers, office assistants, patient coordinators, etc. The program will be offered free to teams, with the understanding that those participating will complete the educational and data collection components.

Participants will be strongly encouraged to complete an interprofessional, standardized, evidence-based, education program, namely Pallium Canada’s LEAP course (Learning Essential Approaches to Palliative care), prior to starting CAPACITI. LEAP is the most widely recognized palliative care education program for generalist health care providers in Canada [14, 15, 20]. Some topics include the palliative care philosophy and complex management for common symptoms such as pain, delirium, constipation, depression, grief, etc. The courses are taught in-person, or via fully online or hybrid delivery, by certified program facilitators [16]. Studies have shown that the LEAP courses provide primary health care teams with foundational skills that allow them to integrate primary palliative care in their clinics [18].

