### Data analysis

The unit of analysis will be the PCP team. Survey (quantitative) data will be used to compare treatment groups with respect to team and individual characteristics (potential covariates) by tabulation methods (means, standard deviations, frequencies). Both team level variables (e.g., region) and member level variables (e.g., palliative care training) will be tabulated. The primary analysis will be a between treatment comparison of intervention and control groups of the change in pre versus post module scores on the primary outcomes (EPCS and % identified for palliative care). Secondary analyses will include comparisons of all team outcomes. Mixed model ANOVA methods will be used, taking into account the increased variance due to cluster randomization, for the assessment of the primary outcomes [30]. Multilevel mixed models with two levels, cluster and repeated measures will be used to investigate the effect of the intervention over time (baseline, post module, 6 months post module).

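### The percentage identified is a count out of a caseload but is analysed as a constant-variance score: valid, but it can give up precision that a count model on the same data would recover

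*Protocol article*

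**What the plan says.** The Primary outcomes section of the protocol article builds the access outcome from the self-reported "number of patients in caseload and number (calculated %) reported as Identified as requiring a palliative approach to care in last 3 months". Table 2 lists the same two parts: "Access: Total case load, # identified PC". So the numerator and the denominator are both on file for each respondent.

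The Data analysis section makes the primary comparison on the "change in pre versus post module scores on the primary outcomes (EPCS and % identified for palliative care" and names the model: "Mixed model ANOVA methods will be used, taking into account the increased variance due to cluster randomization, for the assessment of the primary outcomes". It also says "The unit of analysis will be the PCP team". No weighting, transformation, binomial or count model is mentioned.

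The sample size section treats the percentage as a continuous score. It states "Given a two-sided alpha of 0.05, a power of 80%, 192 providers from 48 teams would be required" for the EPCS subdomain and adds that this size allows "detection of a 1-point difference increase of the % of patients identified as requiring a palliative approach to care (SD = 2".

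On who reports a caseload, the Eligibility section says that participants "can include physicians, nurses, social workers, office assistants, patient coordinators, etc", and the Recruitment section lets solo providers enrol as well as teams. The article gives no mean caseload, caseload spread or baseline percentage.

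**The concern.** The sampling variance of a proportion out of a caseload of n is about p(1-p)/n, so it depends on n. An ANOVA of raw percentages with one residual variance ignores this. A single additional patient moves the percentage by 5 points in a caseload of 20 and by 0.1 point in a caseload of 1000, while the target difference is 1 point. If caseloads are small or uneven, the least precise values inflate the error term and a few extreme percentages can have a large influence. Taking a raw change score adds the chance variation of the pre-module percentage to that of the post-module one.

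The article names this method for a primary outcome, so the point concerns a stated choice and not a detail left open. What is at stake is precision on one of the two outcomes that set the sample size.

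**Working it through.** **1. The plan's own figure.** Inputs from the sample size section: difference 0.5 SD, two-sided alpha 0.05, power 80%, intra-team correlation 0.15, 4 members per team.
- Design effect: 1 + (4 - 1) × 0.15 = 1.45.
- A two-sample t-test needs 64 per arm. 64 × 1.45 = 92.8, and 92.8 / 4 = 23.2, so 24 teams per arm: 48 teams, 192 providers. This matches. (The normal approximation gives 63 per arm, then 23 teams per arm: 46 teams, 184 providers.)
- For the percentage, 1 / 2 = 0.5 SD, the same standardised effect and so the same size.
- Power at 96 per arm: effective n = 96 / 1.45 = 66.2; 0.5 × √(66.2 / 2) = 2.877; Φ(2.877 - 1.96) = 82.0%.
- At the anticipated 100 teams of 4 (200 per arm): 200 / 1.45 = 137.9; 0.5 × √(137.9 / 2) = 4.152; Φ(4.152 - 1.96) = 98.6%.

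**2. Chance variation in one percentage.** SD in points = 100 × √(p(1-p)/n). The true percentage is an assumption. At 3%, the SD is 3.8 for n = 20, 2.4 for n = 50, 1.2 for n = 200 and 0.5 for n = 1000. Chance alone reaches an SD of 2 at n = p(1-p) / 0.02²: 49 at 2%, 73 at 3%, 119 at 5%. For a change score with independent pre and post windows the variance doubles, so at 3% the caseload is 2 × 0.0291 / 0.0004, about 146.

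**3. Gain from weighting, with the SD held at the plan's 2 points.** Assumed grid: baseline 1, 3, 5 or 10%; mean caseload 50, 200 or 1000; lognormal caseloads with CV 0.5, 1.0 or 1.5; 96 per arm; design effect 1.45. In 16 of the 36 cells binomial noise alone exceeds an SD of 2, so they are infeasible. In the other 20, equal weighting has 82.0% power and optimal inverse-variance weighting has 82.0% to 95.0% (relative efficiency 1.00 to 1.57), a gain of 0 to 13 points. Examples:
- 3%, mean 1000, CV 1.0: 82.0% v 82.6%
- 3%, mean 200, CV 1.0: 82.0% v 91.4%
- 10%, mean 1000, CV 1.5: 82.0% v 95.0%

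Weighting purely by caseload gives 38% to 94% and falls below 82% in 16 of the 20 feasible cells. It is therefore not the remedy.

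**4. Simulation of the models.** Assumptions: 48 teams of 4, 3% v 4%, between-provider CV 0.5, team correlation 0.15 on the log-rate scale, lognormal caseloads. Both models were fitted by GEE.

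| Median caseload, log-SD | Post-module only: raw % v negative-binomial with offset | Planned change score v negative-binomial with offset and pre-module rate |
|---|---|---|
| 200, 1.0 | 72% v 78% | 86% v 99% |
| 100, 1.2 | 56% v 74% | 56% v 95% |
| 1000, 0.3 | 87% v 87% | 100% v 100% |

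False-positive rates were 3-6% (middle column) and 5.5-7% (right column), similar for both models. Monte Carlo error in the middle column is about 3 points; a rerun gave 73 v 79, 58 v 74 and 87 v 87. The right column combines two changes, the count model and baseline adjustment in place of a change score. It also assumes that each provider's underlying rate is stable apart from the effect, which favours the adjusted model. Further simulations of the same contrast, including unstable rates and rates linked to caseload, gave for example 89% v 100%, 54% v 90%, 48% v 65% and 100% v 100% at 48 teams. The count model had equal or higher power in every power scenario.

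**5. At 100 teams.** Raw-percentage power on post-module values is 96%, 87% and 99.6% for the three rows. For the second row, the planned change score gives 85% and the adjusted count model 100%.

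**The case against.** The strongest case against is that nothing here is invalid and that the plan keeps its promise on its own terms. An SD of observed percentages already contains the binomial noise, so if 2 is right for the variable tested, the raw-percentage analysis has its stated power. That stands.

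A reader might infer that caseloads are known to differ widely and that the trial therefore falls short of 80% power. The article supports neither. It lists professions and allows solo providers, which makes uneven caseloads plausible, but it gives no caseload figure. The simulated powers below 80% also partly reflect a larger SD than the plan's. The median-200 setting implies SDs of about 2.2 and 2.7 points in the two arms, and the median-100 setting about 2.7 and 3.3. Only the contrast within each cell bears on the choice of model, and the data were generated on the log-rate scale that the count model assumes.

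Equal weighting is also a legitimate target. Randomization is by team and the aim concerns provider and team behaviour, so an equal-weight average answers a sensible question in the percentage points used for sizing. With the team as unit, the article does not say whether members' percentages are averaged or their counts pooled, so equal weight for each member is one reading.

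Finally, model detail is often left to an analysis plan that is not shown here. That does not dispose of the point, because the article does name the variable and the model, and its only variance allowance is for clustering.

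**Conclusion.** The point holds as one of efficiency, not validity. The stated method ignores a denominator that the trial collects. Against a model that uses it, the loss runs from none (large, similar caseloads) to substantial (small or widely varying ones). With the SD held at 2 and 192 providers, it is 0 to 13 points of power against optimal weighting. The simulated gaps reach 39 points (56% v 95%), but only when the change score is also replaced by baseline adjustment, with stable rates and an SD above 2. At the anticipated 100 teams the loss is smaller, and the plan's own inputs give 98.6%. All of these sizes rest on assumed caseloads and baseline percentages. The change is still worth making, because in the scenarios examined the count model never had lower power and it needs no new data.

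**What to change.** In the Data analysis section, replace the mixed-model ANOVA of the change in percentage, for this outcome only, with an overdispersed count mixed model for the number identified. This can be negative-binomial with log(caseload) as offset, or beta-binomial with the caseload as denominator. Include a random team effect, arm, and the pre-module rate as covariate instead of a raw change score. Report the model-based difference in percentage points beside the rate ratio, so that the result can be read against the 1-point target. Keep the equal-weight percentage analysis, adjusted for the pre-module percentage, as a sensitivity analysis.

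The cost is analysis wording. The downsides are that the test is on a ratio scale, so the percentage-point difference has to be derived from the model, and that larger caseloads carry somewhat more weight than in an equal-weight average of providers or teams. The sensitivity analysis shows whether that matters.

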#### Qualitative analysis (focus group data)

We will conduct a thematic analysis using a constant comparison method along a 4-stage process based on Pope’s Framework Approach [31], as we have done previously [32, 33]: 1) Focus groups will be audio taped and transcribed into a document, along with staff notes, for analysis. 2) The Focus group questions will be used to create a template for organizing each team’s data and emerging ideas. 3) Emerging ideas from each template construct will be coded and compared within and across teams, first independently by two analysts and then conjointly. Emerging themes will be compared and discussed until consensus is obtained between the analysts. 4) Common themes for each construct will be identified. We will maintain an audit trail that documents and justifies decisions in the analysis to promote consistency [34].

#### Evaluative framework

We will use the Kirkpatrick Model, a globally recognized training evaluation framework, to frame the various program evaluation components (Table 2). This model outlines 4 critical domains of an effective training program [35]:Reaction: The participant’s reaction or satisfaction to the education program.Learning: The participant’s acquired knowledge and skills from the education program.Behaviour: The participant’s application of what they learned during the program to their practice.Results: The direct outcomes, e.g., patient outcomes, that occur as a result of the education program.

## Discussion

This study protocol details the implementation and evaluation of CAPACITI, a training intervention for guiding generalist health care providers to operationalize a palliative approach to care in primary care practice. The findings from this large-scale, national cRCT will contribute to the evidence base on how to strengthen the ability of primary care physicians, nurses, and other providers to identify and manage their patients requiring palliative care, and in turn, build capacity for this care in the health care system. In particular, we will assess the utility of a facilitated approach to training education. CAPACITI was developed on the premise that context-relevant practice supports are vital to impacting provider behavior, based on knowledge translation science showing that education or tools alone do not change practice without context-relevant information [36–38].

One of the features of this intervention is that it aims to build capacity among interprofessional primary care providers in the community. Doing so does not preclude the need for specialist palliative care in the community but rather recognizes that not all patient needs require secondary level palliative care by specialist teams [3, 4, 39, 40] As such, the program strengthens community-based palliative care capacity within the existing team and health system, capitalizing upon existing expertise, without the need for new front-line human resources or the implementation of formalized system structures [18]. Thus, any built-capacity is more likely to be sustained beyond the program.

Our CAPACITI trial will help address a lack of high-level evidence on knowledge and behavior change in palliative care education for generalist providers using a virtual format with case-based, facilitation. A recent systematic review of trials identified 22 palliative care education interventions for health care providers [21]. Many of these initiatives focused on illness communication or symptom management rather than a wider array of skills to implement a holistic palliative approach to care. As well, most studies focused on a single provider type rather than an interdisciplinary team. Overall, published reviews have concluded that while interactive education inventions for health care providers show potential for building palliative care capacity among generalists, further trial-based evidence is required, especially among virtually delivered programs [41–44].

The proposed CAPACITI cRCT has several conceptual and methodological strengths to be considered. Many previous randomized trials on palliative care education had small sample sizes (20 to 40 per arm) and/or selected participants from a single site [21]. Whereas we expect to enroll a relatively large number of participants, over 200 PCPs per arm, from teams across Canada. This will help ensure that our study has sufficient analytical power, and that the findings are generalizable, at least to other locales in this country. We have designed the program to be virtual (materials and discussions) so that it is scalable, accessible, and cost-effective to implement. The learning management system (Moodle) will allow all participants in the trial to have access to the education materials and enable us to deliver the program to the anticipated 100 + teams that enrol. Moreover, the virtual platform allows teams and providers in rural and remote areas to access the program, overcoming the barriers of travel and geography.

### Limitations

This study has some foreseeable limitations deserving mention. Both study arms will have access to the CAPACITI education materials and therefore we will not have a randomized group that receives “no-CAPACITI education” to compare. PCPs who sign up to the program but receive no education would be unlikely to complete the study measures. Previous RCTs have found non-interactive or non-facilitated on-line palliative care training modules to be effective at improving Palliative care knowledge [45] or attitudes [46] in palliative care. Therefore, it is possible that both arms in the current study will experience a positive effect, the difference which may be negatable between arms, post intervention. Secondly, as typical with RCTs of training interventions, participants will be aware which study arm they have been allocated. We deemed it unfeasible to blind participants to the group arms. The use of self-reported measures presents another limitation as these may be biased toward behaviour change. More objective measures of practice change, such as patient outcomes and administrative data, are warranted but obtaining these data present challenges without existing systems that collect this information. The impact of patient reported outcomes and health service utilization at end of life could be examined in future research. To help validate the quantitative outcomes we will explore the impact of CAPACITI from a qualitative perspective of the PCPs.

## Conclusions

CAPACITI is a unique education program for generalist PCPs in that this intervention is interdisciplinary and comprehensive, as well as virtual. Through this cRCT we will ascertain the added benefit of a facilitated approach to the delivery of education materials, towards informing the most efficient means of translating this knowledge to practice among PCPs and other health care providers. The findings from this health provider education trial may also be applicable to non palliative care specialists and health care providers in tertiary settings.

## Data Availability

This is a study protocol from which no data are available.

## Abbreviation

PCP: Primary Care Provider
